## Abstract

**Background:**

Chronic subdural haematoma (CSDH) is a common neurological disease with a rapidly rising incidence due to increasing age and widespread use of anticoagulants. Surgical intervention by burr-hole craniotomy (BHC) is the current standard practice for symptomatic patients, but associated with complications, a recurrence rate of up to 30% and increased mortality. Dexamethasone (DXM) therapy is, therefore, used as a non-surgical alternative but considered to achieve a lower success rate. Furthermore, the benefit of DXM therapy appears much more deliberate than the immediate relief from BHC. Lack of evidence and clinical equipoise among caregivers prompts the need for a head-to-head randomised controlled trial. The objective of this study is to compare the effect of primary DXM therapy versus primary BHC on functional outcome and cost-effectiveness in symptomatic patients with CSDH.

**Methods/Design:**

This study is a prospective, multicentre, randomised controlled trial (RCT). Consecutive patients with a CSDH with a Markwalder Grading Scale (MGS) grade 1 to 3 will be randomised to treatment with DXM or BHC. The DXM treatment scheme will be 16 mg DXM per day (8 mg twice daily, days 1 to 4) which is then halved every 3 days until a dosage of 0.5 mg a day on day 19 and stopped on day 20. If the treatment response is insufficient (i.e. persistent or progressive symptomatology due to insufficient haematoma resolution), additional surgery can be performed. The primary outcomes are the functional outcome by means of the modified Rankin Scale (mRS) score at 3 months and cost-effectiveness at 12 months. Secondary outcomes are quality of life at 3 and 12 months using the Short Form Health Survey (SF-36) and Quality of Life after Brain Injury Overall Scale (QOLIBRI), haematoma thickness after 2 weeks on follow–up computed tomography (CT), haematoma recurrence during the first 12 months, complications and drug-related adverse events, failure of therapy within 12 months after randomisation and requiring intervention, mortality during the first 3 and 12 months, duration of hospital stay and overall healthcare and productivity costs. To test non-inferiority of DXM therapy compared to BHC, 210 patients in each treatment arm are required (assumed adjusted common odds ratio DXM compared to BHC 1.15, limit for inferiority < 0.9). The aim is to include a total of 420 patients in 3 years with an enrolment rate of 60%.

**Discussion:**

The present study should demonstrate whether treatment with DXM is as effective as BHC on functional outcome, at lower costs.

**Trial registration:**

EUCTR 2015-001563-39. Date of registration: 29 March 2015.

**Electronic supplementary material:**

The online version of this article (10.1186/s13063-018-2945-4) contains supplementary material, which is available to authorized users.

## Background

A chronic subdural haematoma (CSDH) is a common neurological disease with a rapidly rising prevalence due to increasing age and the widespread use of anticoagulants [1–4]. It generally affects the elderly population and patients with coagulopathy, who often have co-existing medical diseases [1, 5]. The estimated incidence in Western countries is 8.1 per 100,000 per year in patients aged 65 years or older [6], but increases to 58/100,000/year for those aged 70 years or older [1, 7].

Surgical intervention by burr-hole craniotomy (BHC) followed by subdural drainage is the mainstay treatment in symptomatic patients with a CSDH [8, 9], which leads to a favourable functional outcome in 84% of patients [10]. However, despite the optimisation of techniques surgery is still associated with relevant complications, recurrence rates up to 30%, and considerable mortality [8–12]. In addition, especially advanced age and the presence of comorbidities could render patients ineligible for BHC.

Dexamethasone (DXM) therapy has been proposed as an alternative, non-operative or adjuvant treatment modality and might have the potential to block the anti-inflammatory changes in the formation of the haematoma and can specifically impede the formation of neo-membranes and neo-capillaries by its powerful inhibition of inflammatory mediators [13, 14]. Therefore, DXM is administered routinely in various institutions.

To date, only three retrospective and one prospective study have compared the clinical effect of DXM to BHC in CSDH patients [15]. To date, no randomised trials have been published that compare both treatments. Therefore, we designed the DECSA trial: a randomised controlled, multicentre trial to evaluate the non-inferiority of primary DXM compared to primary BHC on functional outcome and cost-effectiveness in patients with symptomatic CSDH.

## Methods/Design

### Trial design

This is a prospective, multicentre, open-label, randomised controlled trial (RCT) with a blinded endpoint (PROBE design) assessment [16]. Eligible patients are randomised to DXM therapy (the intervention arm) or BHC (control arm; see Additional file 1 for SPIRIT check-list).

### Primary study objective

The primary objective is to evaluate the non-inferiority of primary DXM therapy versus primary BHC on functional outcome as expressed by modified Rankin Scale (mRS) score (Table 1) at 3 months and cost-effectiveness at 12 months in patients with symptomatic CSDH.

**Table 1 Tab1:** Modified Rankin Scale (mRS)

Score	Functional status
0	No symptoms
1	No significant disability. Able to carry out all usual activities despite some symptoms
2	Slight disability. Able to look after own affairs without assistance, but unable to carry out all previous activities
3	Moderate disability. Requires some help, but able to walk unassisted
4	Moderately severe disability. Unable to attend to own bodily needs without assistance, and unable to walk unassisted
5	Severe disability. Requires constant nursing care and attention, bedridden, incontinent
6	Dead

### Secondary objectives

The secondary objectives of the study are functional and clinical outcome, expressed by mRS and Markwalder Grading Scale (MGS) scores (Table 2), respectively, at discharge, at 2 weeks, 3, 6 and 12 months and Glasgow Outcome Scale-Extended (GOSE) score (Table 3) at 3 months. Furthermore, assessment of quality of life using the Short Form – 36 Health Survey (SF-36) and Quality of Life after Brain Injury Overall Scale (QOLIBRI) will take place at 3 and 12 months and healthcare and productivity costs at 3 and 12 months. Haematoma thickness will be evaluated after 2 weeks on follow-up computed tomography (CT). Mortality will be evaluated during the first 3 and 12 months. During the total follow-up period of 12 months we will also evaluate haematoma recurrence, complications and drug-related adverse events, failure of therapy after randomisation and requiring intervention, duration of hospital stay and overall healthcare and productivity costs.

**Table 2 Tab2:** Markwalder Grading Scale

Score	Clinical status
0	Patient neurological normal
1	Patient alert and oriented; mild symptoms such as headache; absent or mild neurological deficit such as reflex asymmetry
2	Patient drowsy (defined as Glasgow Coma Scale (GCS) score: 13–14) or disoriented with variable neurological deficit, such as hemiparesis
3	Patient stuporous (defined as GCS 9–12) but responding appropriately to noxious stimuli; severe focal signs such as hemiplegia
4	Patient comatose (GCS 8 or lower) with absent motor responses to painful stimuli; decerebrate or decorticate posturing

**Table 3 Tab3:** Glasgow Outcome Scale-Extended

Score	Category
1	Death
2	Vegetative state
3	Severe disability, lower
4	Severe disability, upper
5	Moderate disability, lower
6	Moderate disability, upper
7	Good recovery, lower
8	Good recovery, upper

### Study setting and participants

Patients will be recruited for the study from the emergency department, neurological or neurosurgical outpatient clinic or ward or through referral from general hospitals of the seven participating Dutch neurosurgical hospitals. The seven participating neurosurgical hospitals are Haaglanden Medical Centre (HMC) The Hague, Haga Teaching Hospital The Hague, Leiden University Medical Centre (LUMC) in Leiden, Medisch Spectrum Twente (MST) Enschede, Erasmus Medical Centre (EMC) Rotterdam, Isala Hospital Zwolle and University Medical Centre Groningen (UMCG). The study is open to additional participating neurosurgical centres.

### Inclusion criteria

Eligible patients must be 18 years or older and meet all of the following criteria:The presence of a newly diagnosed CSDH, defined as an isodense or hypodense haematoma in the subdural space on cranial computed tomography (CT) scan. Hyperdense components may be present but must compromise less than one third of the haematomaClinical symptoms must be explained by the CSDHThe patient is eligible for BHC and DXM based on clinical symptoms and radiological appearance of CSDHMGS grade 1–3.

The MGS is a validated grading system (score 0–4, see Table 2) for the severity of neurological symptoms and is used to classify the neurological condition for CSDH patients [17].

### Exclusion criteria

Exclusion criteria are:MGS grade 0 or 4An acute subdural haematomaThe presence of a minimal CSDH on cranial CT which is technically not drainable by BHCPregnancyCerebrospinal fluid shunt in situ (e.g. ventriculoperitoneal shunt)Known hypersensitivity to DXMKnown ulceration in the gastro-intestinal tractPoorly regulated diabetes mellitus (DM) defined as a glycosylated haemoglobin (HbA1C) value > 8% (64 mmol/mol)Clinical suspicion of an acute systemic infection (fever, leucocytosis, elevated C-reactive protein)History of gastro-intestinal bleedingGlaucomaPrevious history of severe affective disorders (i.e. psychosis).

### Participant timeline

The time schedule in Fig. 1 describes all study processes, assessments and interventions. The flow diagram (Fig. 2) displays the main study procedures, including follow-up evaluations.

**Fig. 1 Fig1:**
[figure not shown]
Time schedule of study procedures

**Fig. 2 Fig2:**
[figure not shown]
Flow diagram of main study procedures

In summary, study patients will be evaluated at presentation (baseline), during their hospital stay, at discharge and during the follow-up period at 2 weeks, 3 months, 6 months and 12 months.

At 2 weeks (after initiation of the study treatment) patients will be evaluated by neurological examination combined with a follow-up CT scan at the outpatient clinic or ward and at 3 months at the outpatient clinic. A mRS-certified research nurse, blinded for treatment allocation, will evaluate the primary outcome (mRS score) at 3 months by phone. At 3 and 12 months, patients will receive questionnaires on quality of life. Additionally, an evaluation of mRS score will take place by phone at 3, 6 and 12 months. Healthcare and productivity costs will be evaluated at 3 and 12 months. We expect to complete patient inclusion in 3 years. The estimated duration of the study (including follow-up) will be 4 years.

### Interventions

#### Investigational treatment

Patients in the intervention arm will receive DXM in a daily dosage of 16 mg (8 mg every 12 h) on days 1 to 4. Thereafter, DXM will be tapered by half every 3 days (see Table 4 for the DXM dosing scheme) until a dosage of 0.5 mg a day on day 19 and stopped on day 20. DXM is administered orally in tablets or intravenously when oral administration is not possible. If the patient improves on DXM therapy (defined by ≥ 1 point decrease in MGS score) during the first 2 weeks, the treatment will be continued until day 19. During DXM treatment a proton pump inhibitor (pantoprazole, 40 mg daily) is administered as prophylaxis.

**Table 4 Tab4:** Dexamethasone (DXM) dosing scheme

Day	DXM dosage
1–4	8 mg every 12 h
5–7	4 mg every 12 h
8–10	2 mg every 12 h
11–13	1 mg every 12 h
14–16	0.5 mg every 12 h
17–19	0.5 mg per day
20	Stop

DXM therapy can be discontinued for the following reasons: (1) no improvement of the clinical condition, defined as an unchanged MGS score 2 weeks after initiation of DXM therapy with unchanged or increased haematoma on the follow-up CT at 2 weeks, (2) clinical deterioration, defined by as ≥ 1 point increase in MGS score, at any time after initiation of DXM treatment, (3) the occurrence of severe, relevant DXM-related side effects or complications (i.e. uncontrollable hyperglycaemia, gastro-intestinal bleeding or psychiatric symptoms), (4) pre-study complement discontinuation of DXM therapy is primarily left to the discretion of the treating physician and is recommended in case of: persistence of moderate to severe neurological symptoms (MGS grade 2–3) in combination with the presence of relevant severe, current comorbidities (i.e. an infection, metabolic deterioration) which could interfere with the expected recovery, and a surgical intervention could be beneficial and the safest option for patient recovery.

In any case of pre-study discontinuation of DXM therapy, the reason for this is documented. Whenever DXM is discontinued, a cross-over to the reference treatment (BHC) can occur depending on the remaining symptoms, which is the local standard of care in the participating hospitals.

#### Reference treatment

Patients randomised to the reference treatment arm are operated on preferably within the first 7 days, depending on anticoagulant or antithrombotic therapy use, severity of symptoms and discretion of the treating physician. Surgery will take place through BHC followed by insertion of a subdural drain for 2 days in line with the standard protocols in each participating hospital. Antibiotic prophylaxis is administered preoperatively. Either general or local anaesthesia will be applied. One or two 14-mm burr holes, depending on the surgeon’s discretion, are drilled over the maximum width of the haematoma. The dura mater is opened with a cruciate incision and coagulated with bipolar diathermy. The subdural collection is washed out with warm Ringer’s lactate saline, with or without a catheter. The subdural outer and inner membrane loculations, if present, can be disrupted when easily accessible via the burr holes. Whenever the saline has dispersed sufficiently a subdural drain is placed and the wound is closed.

Reoperation can be indicated when neurological deficits do not resolve, deteriorate or recur within the follow-up duration. Treatment options consist of redo burr-hole evacuation, if necessary, through another additional hole, percutaneous aspiration, craniotomy, or craniectomy.

#### Concomitant care

All included patients will otherwise receive routine standard of care. Patients with mild neurological deficits (MGS grade 1) on admission can be discharged home in anticipation of the planned BHC or awaiting the effect of DXM therapy. However, in MGS grade 1 patients with known diabetes mellitus (DM) with HbA1C < 64 mmol/mol randomised for DXM therapy, monitoring for blood glucose levels is necessary during the first 3 days after treatment initiation. Glucose monitoring can take place clinically during admission or if possible at the nursing home. Patients with MGS grade 2–3 (in either arm) remain in hospital until the treating physician judges the clinical situation safe for discharge.

During admission neurological investigations and vital parameters are recorded daily. Low-molecular-weight heparin (LMWH) will be applied in both patient groups as thrombosis prophylaxis if the patient is not optimally mobile. Patients will receive physiotherapy, speech therapy or rehabilitation consultation if deemed necessary.

##### Anticoagulant or antithrombotic therapy

Oral anticoagulant or antithrombotic therapy will be discontinued in both study arms from the moment of randomisation to prevent haematoma growth and to avoid interference with planned surgery. In case of vitamin K antagonist (VKA) therapy the international normalised ratio (INR) is corrected to ≤ 1.5 through the administration of vitamin K and/or prothrombin complex concentrate (PCC), as is the current practice. For patients using platelet-aggregation-inhibitor therapy, surgery is preferably planned 7 days after discontinuation of therapy, if allowed by the clinical condition. At the discretion of the surgeon, earlier intervention is allowed if deemed clinically necessary. The reason for early surgery has to be recorded in the case report form (CRF). Non-vitamin-K oral anticoagulants (NOACs) are discontinued at least 1 day prior to surgery.

Any anticoagulant or antithrombotic therapy can be resumed 2 weeks after the initiation of DXM therapy or surgery following a follow-up CT without signs of CSDH recurrence, recent-onset haematoma or unchanged mass effect with midline shift compared to the initial CT at randomisation. Partial resolution of CSDH at this stage without recent haematoma is not a contraindication for resumption. For absolute indications (e.g. mechanic cardiac valve) earlier resumption or bridging of therapy within these 14 days is allowed. Any reason for early resumption has to be recorded in the CRF. Subgroup analyses will be performed to evaluate the effect of anticoagulant therapy in both groups.

### Outcomes

#### Primary outcome measures

The primary endpoints are the functional outcome, expressed by mRS, at 3 months after start of study treatment and cost-effectiveness at 12 months.

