#### Secondary outcome measures

Secondary outcomes include: functional and clinical outcome, expressed by mRS and MGS scores, respectively, at discharge, at 2 weeks, at 3, 6 and 12 months after start of study treatment. We will also determine a utility-weighted mRS (UW-mRS) at 3 months. The GOSE score will be assessed at 3 months, quality of life (expressed by SF-36 and QOLIBRI) at 3 and 12 months, cost-effectiveness at 3 and 12 months and haematoma thickness at 2 weeks. During the first 12 months, we will evaluate haematoma recurrence (defined as recurrence of symptoms and neurological signs after initial improvement with persistence, recurrence or increase of CSDH on follow-up CT), failure of therapy after randomisation and requiring intervention, complications and drug-related adverse events, duration of hospital stay and healthcare and productivity costs in both patient groups. Finally, we will evaluate mortality during the first 3 and 12 months.

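### The 3-month mRS is timed from start of treatment, which can come up to about a week later after randomisation for surgery than for dexamethasone; time it from randomisation

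*Protocol article*

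**What the plan says.** Under Primary outcome measures, the Protocol article gives the primary endpoints as the mRS "at 3 months after start of study treatment and cost-effectiveness at 12 months". Secondary outcome measures repeats the mRS and the Markwalder grade (MGS) "at 3, 6 and 12 months after start of study treatment". Participant timeline uses the same origin for the early visit: "At 2 weeks (after initiation of the study treatment) patients will be evaluated by neurological examination".

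The time from randomisation to that origin is set separately for each arm:

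- **BHC.** Reference treatment says patients are "operated on preferably within the first 7 days, depending on anticoagulant or antithrombotic therapy use". This is a preference with no hard limit, and the text does not say from when the days are counted.
- **BHC in platelet-inhibitor users.** Under Anticoagulant or antithrombotic therapy, "surgery is preferably planned 7 days after discontinuation of therapy", if the clinical condition allows. The same section says oral anticoagulant or antithrombotic therapy "will be discontinued in both study arms from the moment of randomisation".
- **DXM.** Investigational treatment numbers the treatment days from 1 but does not relate day 1 to randomisation. No wait is described.

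Data analysis compares the arms by intention-to-treat on all randomised patients and excludes those whose primary outcome is missing. One outcome has a different origin: the Abstract lists "failure of therapy within 12 months after randomisation and requiring intervention". Mortality, recurrence and costs are given windows in months without a stated origin.

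**The concern.** An intention-to-treat comparison needs a clock that starts at the same point in both arms and exists for every randomised patient. Randomisation provides this. Start of treatment does not: it happens afterwards, it depends on the allocated arm, and in some patients it may never happen.

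Two consequences follow from the text as written. First, patients in the BHC arm who wait for surgery are assessed later after randomisation than patients who start DXM promptly. The treatment contrast at 3 months is then partly a contrast between two assessment times. Second, a patient who recovers or withdraws before any treatment has no date from which to count 3 months, yet belongs to the analysis set. Because patients with a missing primary outcome are excluded, an undefined date could turn into an exclusion.

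The non-inferiority limit is an odds ratio of 0.9, which is narrow. Avoidable differences in timing between the arms are worth removing for that reason.

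**Working it through.** The plan gives no figure for the interval from randomisation to treatment in either arm, so there is no figure of its own to reproduce. What can be computed is the shift in assessment day.

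**Inputs**

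- Visits at 2 weeks and 3, 6 and 12 months, taken as 14, 91, 182 and 365 days after start of treatment.
- DXM start: not stated; assumed day 0 after randomisation.
- BHC start: antithrombotics stop at randomisation (day 0), and surgery in platelet-inhibitor users is preferably 7 days after the stop. Planned surgery in these patients is therefore at about day 0 + 7 = day 7. Other patients may be operated on sooner.
- Range for the wait: 3, 7 and 14 days. The 14-day value is an assumed upper case, used because 7 days is only a preference.

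**Formula.** Day of assessment after randomisation = wait + visit day. With DXM at day 0, the relative delay in the BHC arm = wait / visit day.

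| BHC wait | 2 weeks | 3 months | 6 months | 12 months |
|---|---|---|---|---|
| 3 days | 17 vs 14 (21.4%) | 94 vs 91 (3.3%) | 185 vs 182 (1.6%) | 368 vs 365 (0.8%) |
| 7 days | 21 vs 14 (50.0%) | 98 vs 91 (7.7%) | 189 vs 182 (3.8%) | 372 vs 365 (1.9%) |
| 14 days | 28 vs 14 (100%) | 105 vs 91 (15.4%) | 196 vs 182 (7.7%) | 379 vs 365 (3.8%) |

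Each cell gives the BHC day against the DXM day. If DXM starts on day 1, the 7-day case shrinks to a 6-day difference at 3 months: 98 against 92, or 6/92 = 6.5%.

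**Scale against the margin (illustration only).** The margin on the log scale is |ln 0.9| = 0.105. Suppose the mRS were still improving near month 3 by 0.05 to 0.2 log-odds per 30 days in both arms. A mean lag of 7 days would then shift the log odds ratio by:

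- 0.05 × 7/30 = 0.012, or 11% of the margin;
- 0.2 × 7/30 = 0.047, or 44% of the margin.

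The trend is not in the document and could be flat or negative. These figures show only that a week is not obviously negligible against this margin. They do not estimate the bias.

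**The case against.** The strongest reply is that the arms are aligned on time since treatment, which is clinically natural, and that a week in about 13 changes little. This is partly right. The 7-day target applies only to platelet-inhibitor users, the non-vitamin-K anticoagulants need only a day, earlier surgery is allowed when clinically necessary, and the interval to treatment is reviewed by the Data Safety Monitoring Board. The average lag may therefore be well below 7 days. It remains a lag produced by allocation, and equal time since treatment is not what an all-randomised comparison is built on.

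A second reply is that the 2-week anchor has a purpose. That stands. Investigational treatment and the antithrombotic section both tie treatment decisions to 2 weeks after treatment start.

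A third is that rules for untreated patients and survival origins may be in the statistical analysis plan, which is not shown. Their absence is therefore not held against the article. The point rests on the origin that the article does state.

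A reader might go further and infer three things that the document does not support:

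- **That events before surgery fall outside follow-up.** The treatment-start wording is attached to the mRS and MGS assessments and the 2-week visit. Adverse events are recorded throughout the study, failure of therapy counts from randomisation, and a death before surgery is still mRS 6 at 3 months.
- **That the survival comparison contains immortal time, or that costs of waiting are dropped.** The mortality and cost windows have no stated origin. They are not set at surgery.
- **That the timing favours BHC.** This needs continuing improvement near month 3, for which no figure is given. If it did favour BHC, non-inferiority of DXM would be harder to claim, not easier.

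Nor are two origins in one document a contradiction in themselves, since a status score and an event outcome can be timed differently.

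**Conclusion.** The point holds in a limited form. The primary mRS and the later mRS and MGS assessments are anchored to a post-randomisation event whose delay depends on the arm. This fits poorly with an intention-to-treat analysis of all randomised patients and leaves never-treated patients without a defined assessment date. How many such patients there will be is unknown.

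Assuming DXM on day 0 and BHC on day 7, the offset is about 7 days: modest for the primary endpoint (7.7%), large only at 2 weeks (50%), and small at 12 months (1.9%). The direction and size of any resulting bias in the common odds ratio cannot be derived from the document. This is an inexpensive improvement worth making, not a flaw that invalidates the trial.

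**What to change.** 1. Time the 3-month (primary), 6-month and 12-month mRS and MGS assessments from the date of randomisation in both arms, and schedule calls and visits from that date. Every randomised patient then has an assessment date, treated or not.
2. State the same origin for the mortality, recurrence, cost and QALY windows, as failure of therapy already has.
3. Leave the 2-week visit and CT tied to treatment start, because treatment decisions use them, and report days since randomisation at that visit by arm.
4. For patients already enrolled, report the actual days from randomisation to the mRS by arm and use them in a sensitivity analysis of the primary odds ratio.

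The cost is a wording amendment to the visit schedule. Randomisation runs in the same Castor system that holds the trial data, so the date should already be available. The one real downside is that BHC patients who wait will have slightly less post-operative recovery time at the 3-month call: with a 7-day wait, 91 − 7 = 84 days instead of 91. That is acceptable, because the wait is part of the strategy to which they were randomised.
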